### Economic evaluation

Health care costs include costs of hospital admissions and readmissions (operation, nursing days, outpatient visits), institutional care (nursing homes, hospice), home care, informal care, medication and other health care providers as well as direct non-medical costs (travel expenses). These costs will be estimated for the period after inclusion until 6 months. Data on hospital care will be collected from the hospital information systems and CRFs. The participating clinicians will fill out CRFs during control visits, re-interventions and admissions. Use of institutional care, home care and other health care providers will be collected with a short checklist, used by a special trained research nurse at 14 days interval until 6 months after inclusion. Informal care after discharge will be registered as time spent on informal care giving. This will be measured using the recall questionnaire as introduced by van den Berg et al[23]. Those questionnaires will be handed out by the patients to their caregivers on week 4, 12 and 24 after inclusion.

Real unit costs will be estimated for the surgical interventions and stent placement on the basis of resource use by detailed measurement of manpower and personnel time, equipment, materials, housing and overhead, following the microcosting method. Costs of inpatient days in hospital will be estimated as real costs per day using detailed information from the financial department of the Academic Medical Center. For all other health care and informal care, unit costs will be estimated following Dutch guidelines using fees and standardized costs if considered representative, and adapted if necessary.

Patient outcome analysis will be expressed by calculating the costs per quality adjusted life-years (QALYs). For this calculation the standardized questionnaire (EQ-5D) will be used as this questionnaire can be translated to utilities with values from the UK general population.

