### Participating centers

Fifteen Dutch hospitals including 4 academic and 11 non academic are currently participating in this trial. Specific requirement is to assure that enteral stent placement is performed by an experienced gastroenterologist. Gastroenterologists are considered experienced after placement of at least 20 enteral stents of which 10 colonic. In case no experienced gastroentorologist is available the patient should be referred to a nearby hospital with sufficient experience. The patient can always be referred for stent placement to the Academic Medical Center in Amsterdam. Laparoscopic sigmoidectomy or stoma creation is allowed if sufficient experience is available (> 20 cases).

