### Final analysis

If the hypothesis holds, a strategy of colonic stenting combined with elective surgery will lead to a better quality of life, less morbidity, mortality and costs compared with the standard strategy of emergency surgery. In that case the effectiveness and costs of both strategies will be reported. If the alternative strategy turns out to be more effective but more costly than the standard treatment, the costs per QALY will be calculated. In a sensitivity analysis, the impact of the statistical uncertainty of major parameters in the cost-effectiveness analysis will be examined. Since costs per patient are typically highly skewed, non-parametric bootstrap techniques will be used to derive a 95% confidence interval for the differences in mean and median costs.

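### The cost per QALY joins Dutch costs to UK health-state preferences, and no stated sensitivity analysis tests that choice

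*Protocol article*

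**What the plan says.** Under Participating centers, the Protocol article states that "Fifteen Dutch hospitals including 4 academic and 11 non academic are currently participating in this trial". No centre outside the Netherlands is mentioned.

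Under Economic evaluation, the costs come from three sources:

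- Interventions: "Real unit costs will be estimated for the surgical interventions and stent placement on the basis of resource use", by microcosting.
- Hospital stay, from the Academic Medical Center's accounts: "Costs of inpatient days in hospital will be estimated as real costs per day using detailed information from the financial department".
- Everything else: "For all other health care and informal care, unit costs will be estimated following Dutch guidelines using fees and standardized costs".

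The same section expresses patient outcome as costs per QALY. It selects the EQ-5D for this because "this questionnaire can be translated to utilities with values from the UK general population". It gives no reason for taking UK rather than Dutch values and names no second value set.

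Final analysis says when the ratio is needed: "If the alternative strategy turns out to be more effective but more costly than the standard treatment, the costs per QALY will be calculated". The sensitivity analysis described there concerns the statistical uncertainty of the main cost-effectiveness parameters. The bootstrap is for confidence intervals on differences in mean and median costs.

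**The concern.** A utility is a preference weight, and it depends on whose preferences were elicited. The numerator of the cost per QALY here is what the strategies cost in Dutch hospitals and Dutch care. The denominator is health gain as the UK public would weigh it. A Dutch decision maker would normally want both sides of the ratio to refer to the same setting, or at least to know whether the answer changes when they do.

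As described, the plan would not show this. Resampling patients, or varying parameters within their sampling error, keeps the scoring table constant. If the economic conclusion turned on the table, none of the stated analyses would reveal it. The Discussion gives the trial's aim as informing whether stenting as a bridge to surgery should be done at all. Where stenting proves better but dearer, the cost per QALY would be the main economic summary.

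**Working it through.** The documents give no utility, QALY or cost figure, so there is no figure of the plan's own to reproduce. The check is a comparison of the stated sources, followed by algebra.

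**Step 1. Which country each ingredient comes from**

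| Ingredient | Stated source | Section | Country |
|---|---|---|---|
| Patients | Fifteen hospitals | Participating centers | Netherlands |
| Surgery and stent placement | Microcosting of resource use | Economic evaluation | Netherlands (the hospitals are Dutch) |
| Inpatient days | Academic Medical Center accounts | Economic evaluation | Netherlands |
| Other health care, informal care | Dutch guidelines | Economic evaluation | Netherlands |
| Utilities | UK general-population values | Economic evaluation | UK |

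Only the utilities come from elsewhere.

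**Step 2. How the value set enters the ratio**

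Cost per QALY = ΔC / ΔQ, where ΔC and ΔQ are the differences between arms in mean cost and mean QALYs. The value set does not affect ΔC. Let r = ΔQ under another value set divided by ΔQ under UK values. Then

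cost per QALY (other set) = cost per QALY (UK) × 1/r.

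The documents give nothing from which to obtain r. Purely to show the scaling, under assumed values:

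| Assumed r | 0.7 | 0.8 | 0.9 | 1.0 | 1.1 | 1.2 |
|---|---|---|---|---|---|---|
| Multiplier 1/r | 1.43 | 1.25 | 1.11 | 1.00 | 0.91 | 0.83 |

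These are not estimates for this trial.

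**Step 3. Why r is not simply the ratio of utility gaps**

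Take two living states A and B with utilities u_A and u_B, and death at 0. Let ΔT be the difference between arms in mean time spent in each state over the common 6-month follow-up, so that ΔT_A + ΔT_B + ΔT_dead = 0. Substituting ΔT_B = −ΔT_A − ΔT_dead gives

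ΔQ = u_A ΔT_A + u_B ΔT_B = (u_A − u_B) ΔT_A − u_B ΔT_dead.

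The first term depends on the gap between living states. The second depends on how far a living state lies from death. A change of value set can rescale the two terms differently. One common factor is therefore adequate only if the arms do not differ in survival, or if both terms happen to scale alike. Mortality is a stated outcome, and Background cites 15–34% for emergency surgery, so the second term cannot be assumed away.

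**Step 4. Whether the stated sensitivity analysis covers it**

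Sampling uncertainty concerns how ΔC and ΔQ vary over repeated samples with the scoring table held fixed. Replacing the table changes what ΔQ is meant to estimate. The cost bootstrap does not involve utilities. Neither analysis tests the choice.

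**The case against.** The strongest reply is that nothing here is wrong or contradictory. A value set is named openly, no passage requires Dutch preferences, and a ratio with its value set stated can still be interpreted. That stands: this is a scoring choice that can be improved, not an error.

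Several stronger readings are tempting, and the documents do not support them.

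- *That only UK values will ever be used.* The sentence explains why the EQ-5D was selected and does not exclude a second scoring. The article is condensed, and a further value-set analysis could be in the full protocol or analysis plan. The point therefore rests on the choice that is stated, not on the absence of detail.
- *That a Dutch set was at hand and was passed over.* The documents do not say whether one existed. UK values may have been the usable option.
- *That all costs follow Dutch guidelines.* Those guidelines govern only other health care and informal care. The remaining costs are real unit costs, though they too come from Dutch hospitals, so the mismatch is unchanged.
- *That the acutely obstructed state makes the value set especially influential.* Under Data collection and monitoring, the EQ-5D is completed on the day of randomization and at weeks 4, 12 and 24. The acute state is measured when the arms are equal in expectation, so its valuation should do little to separate them. How severe the follow-up states are is not known from the documents.

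It is also fair to say that the affected result is narrow. The stated hypothesis is better outcomes at lower cost, and in that case Final analysis has effectiveness and costs reported, with the ratio reserved for the case where stenting is better but dearer. However, Economic evaluation announces costs per QALY without that condition.

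**Conclusion.** The point holds as a modest improvement to a secondary analysis. The named value set is British while the patients and every cost source are Dutch, and the stated sensitivity analysis does not test that choice. This follows directly from the text and needs no numerical assumption.

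The size and direction of the effect cannot be derived from the documents; the multipliers shown above only illustrate the algebra. A reader might infer that the planned ratio would be biased in a known direction, or could not inform Dutch decisions at all. Neither follows: r may be close to 1, and the ratio stays readable so long as the value set is reported with it. The sample size, the primary quality of life analysis on the EORTC scale, and the morbidity and mortality comparisons do not use EQ-5D utilities and are unaffected.

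**What to change.** In Economic evaluation, state that EQ-5D answers will be scored with a Dutch general-population value set in the base case if one is available at the time of analysis. Keep the UK values as a pre-stated sensitivity analysis and report the cost per QALY under both. If no Dutch set is available, keep the UK values and state that limit on the conclusion. Settle this before results are seen, so that the choice of value set cannot appear to have been made for its answer.

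The cost is a second scoring of answers already collected and one extra results row, with no new data, visits or patients. The downside is a slightly less direct comparison with studies that use UK values, which the retained UK analysis covers.

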### Final analysis

If the hypothesis holds, a strategy of colonic stenting combined with elective surgery will lead to a better quality of life, less morbidity, mortality and costs compared with the standard strategy of emergency surgery. In that case the effectiveness and costs of both strategies will be reported. If the alternative strategy turns out to be more effective but more costly than the standard treatment, the costs per QALY will be calculated. In a sensitivity analysis, the impact of the statistical uncertainty of major parameters in the cost-effectiveness analysis will be examined. Since costs per patient are typically highly skewed, non-parametric bootstrap techniques will be used to derive a 95% confidence interval for the differences in mean and median costs.

## Discussion

The concept of colonic stenting as bridge to elective surgery in patients with an acute left-sided malignant colonic obstruction has been developed to reduce the morbidity, mortality and numbers of colostomies. Although some might consider stenting as bridge to surgery the preferred approach, solid evidence is lacking. A previously conducted randomized trial comparing surgery with stenting for incurable left-sided malignant colonic obstruction had to be stopped because of an unexpectedly high number of perforations in the stented group [24]. For this reason, the Stent-in 2 study is conceived to compare colonic stenting as bridge to elective surgery with emergency surgery (current standard treatment) for the management of acute left-sided malignant colonic obstruction. This multicenter randomized study will compare those two strategies with regard to effectiveness and costs. The aim is to provide evidence whether or not colonic stenting as bridge to surgery is to be performed in patients with acute left-sided colonic obstruction.
